## *Expect With Me* group prenatal care

*Expect With Me* group prenatal care was designed based on: (1) principles of group care [35]; (2) evidence from randomized controlled trials demonstrating improved birth outcomes for women receiving prenatal care in a group format [18, 21]; (3) clinical guidelines for prenatal care delivery [36]; and (4) research on patient and provider engagement through social media and technology [37–39]. Designed with national dissemination as a primary consideration, *Expect With Me* incorporates the best evidence-based aspects of existing models of group care [22, 40–42] with a novel IT platform to improve patient engagement and support, enhance health behaviors and decision making, connect providers and patients, and improve health service delivery.

*Expect With Me* provides care to groups of 8–12 women of the same gestational age. Women receiving *Expect With Me* begin prenatal care in the traditional manner. Formal intake (history, exam) is performed at an initial visit prior to group assignment. All prenatal care thereafter occurs within a group setting, except for health issues that require privacy and cervical assessments in late pregnancy. Ultrasounds and laboratory screenings occur per ACOG clinical guidelines [36]. *Expect With Me* is implemented from week 14 of pregnancy (after initial individual assessment) through delivery, following the same schedule as individual care. However, group visits are 90–120 min each, and follow a unique structured curriculum that incorporates the standard content of prenatal care, and emphasizes critical contemporary health issues relevant to pregnancy, such as nutrition, physical activity, stress/mental health, and sexual health. Table 1 summarizes the timing and recommended topics to be covered during each session. Participants may bring their partner, family member, or other support person to group sessions.

**Table 1 Tab1:** *Expect With Me* group prenatal care session timing and topics

Session	Themes	Topics
1 (13–17 weeks)	You’re a healthy mom	• Eat and live healthy for you and your baby • Stay active while you’re expecting • Maintain healthy weight during pregnancy • Understand routine prenatal testing and emergencies • Know what blood pressure and weight numbers are healthy for you

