## Methods/Design

*Expect With Me* is being evaluated via a multisite, longitudinal matched-cohort study, in which data are collected in a real-world settings at the patient and organizational levels. For national scale-up and sustainability, it is essential that the program not only be effective for patients but that the implementation strategy fits with the context of health clinics providing prenatal care [52]. A rigorous multi-method evaluation is being conducted to examine the impact of *Expect With Me* on maternal health and birth outcomes and identify and address barriers to national scalability. Cost analyses are also planned.

The study includes a rigorous process and outcome evaluation. Birth outcomes are the primary study outcomes (e.g., preterm birth, birthweight, neonatal intensive care unit admission/duration). Maternal psychosocial, health behaviors, and health outcomes (e.g., depression, breastfeeding, postpartum weight loss) are secondary outcomes.

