The process evaluation will identify factors that influence uptake, fidelity, and sustainability of *Expect With Me* to inform scalability. We will employ quantitative approaches, such as online surveys and health record reviews as well as systematic qualitative approaches, such as in-depth interviews and focus groups. Key components of comprehensive process evaluations specified by Steckler and Linnan [53] will be adapted to meet the specific needs of this study. Uptake will include reach (number of groups offered); dose delivered (extent to which providers enroll patients and facilitate *Expect With Me* sessions); and dose received (willingness of eligible patients to participate; attendance in group sessions). Fidelity refers to the quality and integrity of the intervention as conceived, and is a function of implementation by clinical sites. We will examine how groups were planned and populated, the content and process of each session, and the perceptions of site staff and patients about *Expect With Me*. We will document whether *Expect With Me* patients received the intended exposure to the intervention, including attendance at each session; proportion of prenatal visits delivered in group; and patient use of IT platform. Sustainability will be driven, in part, by the impact of *Expect With Me* on healthcare costs. We will analyze the impact of birth outcomes on healthcare costs. We will document differences in utilization of care (e.g., emergency department, neonatal intensive care unit) between *Expect With Me* and individual care. Sustainability is impacted by depth of training and satisfaction with *Expect With Me* by providers and staff. We will document penetration of staff trainings and collect feedback from clinical site personnel. These data can be used to scale this intervention, nationally.

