## Data collection and measurement

Both quantitative and qualitative data are being obtained at the organizational and patient levels. Table 2 shows how each of the data collection strategies will be used to assess key study outcomes.

**Table 2 Tab2:** Assessment of key study outcomes

Outcome	Definition	Measure	Data Collection Strategy
Outcome evaluation			
Effectiveness	Impact of *Expect With Me* on patient outcomes	Patient-level - Comparison of birth outcomes between *Expect With Me* patients and the matched cohort who received individual care	- Health record reviews - Patient surveys
Process evaluation			
Uptake	Extent to which providers refer patients to *Expect With Me* and deliver group prenatal care sessions	Organization-level - Number and proportion of providers referring patients for *Expect With Me* during the enrollment period - Number and proportion of providers delivering *Expect With Me* group prenatal care sessions	- Health record reviews
	Willingness of eligible patients to participate in *Expect With Me* and extent to which they are representative of the target population	Patient-level - Number and proportion of eligible patients enrolled in *Expect With Me* - Characteristics of *Expect With Me* participants - Reasons patients participate/do not participate	- Health record reviews - Online tracking system - Patient surveys and focus groups
Fidelity	Extent to which *Expect With Me* is implemented as planned	Organization-level - Conformity to the implementation strategy - Conformity to the implementation content - Amount of sessions/groups completed - Amount of content delivered per session - Clinic staff perception about *Expect With Me’s* content and implementation strategy - Satisfaction about implementation within the clinic Patient-level - Amount of sessions attended - Amount of information technology platform use	- Online tracking system - Session evaluations - Provider interviews and focus groups - Patient surveys and focus groups - Site visits
	Amount of the program received by patients		

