## Analyses

Descriptive analyses of quantitative data will be performed. Women who participated in group prenatal care and those who received individual care will be matched on the basis of propensity scores. Propensity score matching is a statistical technique to correct for observable difference between the treated and non-treated group, thereby reducing selection bias and strengthening causal inferences, in observational studies [60]. We will use multiple imputation and maximum likelihood techniques to handle missing data and sensitivity analyses to assess the robustness of inferences about treatment effects to various missing data assumptions, as needed.

Generalized linear and logistic regression models will be used to analyze continuous (e.g., gestational age at delivery and birth weight) and dichotomous outcomes (e.g., preterm birth, low birth weight), respectively. Negative binomial regression models will be used to analyze count outcomes (e.g., neonatal intensive care unit days). Each model will include a main effect for treatment group (*Expect With Me* vs. individual care). Because many women who attend group prenatal care sessions also supplement with individual visits [61], adjusted models will control for number of individual visits, as well as contain predictor variables that are clinically meaningful to a specific hypothesis of interest.

Trajectories of change for outcomes that are repeatedly measured over time (e.g., weight) will be examined using linear and non-linear mixed effects modeling, with a random effect for subject. An optimal covariance structure will be selected based on the likelihood ratio test for nested models and based on the Akaike Information Criterion for non-nested models [62]. The main independent effects of time, treatment, and second-degree interactions of these predictors will be considered in each model, adjusting for other covariates as described above.

Multilevel mixed models will be used to identify factors that influence primary outcomes among *Expect With Me* patients, with the effect of site modeled as a random effect. A scale variable that will reflect a woman’s attendance level at prenatal care group visits will be created to evaluate whether there is a “dose–response” intervention effect. Structural equation models will be used to examine factors that may mediate the relationship between participation in group care sessions and improved outcomes.

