## Sample size

Results from previous randomized controlled trials suggest that group prenatal reduces likelihood of delivering a preterm or small for gestational age baby by 33–34% [18, 21]. Based on these findings and the national preterm birth rate of 9.6% [4], we need a minimum of 1,768 study participants with one-third (*n* = 884) receiving group prenatal care to have power of .80 to detect differences at alpha = 0.05 with a one-tailed test. With a potential 10% drop out rate due to miscarriage, pregnancy complications and changes in life circumstances (e.g., geographic move), we will recruit 1,000 women, expecting to follow more than 900 of them through one-year postpartum. We will compare primary maternal health and birth outcomes for these women with a 2–1 matched cohort of 2,000 patients receiving individual care. Therefore, the total study sample of women receiving both group and individual prenatal care will include a total of 3,000 women.

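### The planned attendance dose-response analysis has no safeguard against delivery cutting off later sessions, so a plain count of sessions would look protective against preterm birth even with no effect

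*Protocol article*

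**What the plan says.** The Analyses section states: "Multilevel mixed models will be used to identify factors that influence primary outcomes among" Expect With Me patients, with site as a random effect. The same paragraph adds a scale for a woman's "attendance level at prenatal care group visits will be created to evaluate whether there is a" dose-response effect of the intervention. It then says: "Structural equation models will be used to examine factors that may mediate the relationship between participation in group care sessions and improved outcomes".

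The outcomes are set in Methods/Design: "Birth outcomes are the primary study outcomes (e.g., preterm birth, birthweight, neonatal intensive care unit admission/duration".

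The section describing the intervention says that it "is implemented from week 14 of pregnancy (after initial individual assessment) through delivery". Table 1 gives the timetable. Session 8 falls at 33–37 weeks, session 9 at 35–39 weeks and session 10 at 37 weeks or later.

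Two other places bear on how attendance might be measured. Table 2 lists "Amount of sessions attended" as a patient-level fidelity measure. The process-evaluation text in Methods/Design lists "proportion of prenatal visits delivered in group" among the exposure measures. Neither is tied to the dose-response scale. The article states no gestational-age cut-off, no denominator of sessions available before delivery and no time-varying exposure.

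**The concern.** A dose-response analysis needs an exposure that is settled before the outcome. Here the outcome truncates the exposure. A woman who delivers before 37 weeks cannot attend session 10, and with sessions held mid-window she also misses session 9 and possibly earlier ones. Women who deliver at term have time for all or nearly all ten. Low attendance then goes with preterm birth because early delivery removed the opportunity to attend. Covariates and a random site effect do not remove this, because the link runs from outcome to exposure.

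Dividing the count by ten changes only the unit. The test and its bias are the same.

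The study is not randomised, so an attendance gradient could easily be taken as supporting evidence of cause. If the structural equation models use the same attendance variable for birth outcomes, they inherit the problem.

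**Working it through.** The article gives no figure for this analysis, so there is none to reproduce. The check has three steps.

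**1. Sessions available, by gestational age at delivery**

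Window midpoints from Table 1, sessions 1–9: 15, 19, 22.5, 27, 29, 31, 33, 35 and 37 weeks. Session 10 is taken at 38 weeks (assumption; the table says 37+).

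| Delivery (weeks) | Sessions before delivery |
|---|---|
| 30 | 5 |
| 32 | 6 |
| 34 | 7 |
| 36 | 8 |
| 39 | 10 |

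If every session is held at the start or the end of its window instead, delivery at 36 weeks leaves 9 or 7 sessions.

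**2. Simulation with no effect of the intervention**

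Inputs from the article:
- 900 women (Sample size expects to follow more than 900).
- 9.6% preterm; Sample size cites "the national preterm birth rate of 9.6"%.
- The Table 1 timetable.

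Assumptions not in the article:
- Mean attendance per session of 50%, 70% or 90%, varying between women (beta distribution) and unrelated to outcome.
- Preterm deliveries on average 1.5, 2.5 or 3.5 weeks before week 37.
- Term deliveries about 39.2 weeks (SD 1.1).
- No site effect.

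Model: logit P(preterm) = a + b × sessions attended. The odds ratio (OR) per session is exp(b), with a two-sided 5% test and 300 replicates per setting.

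At 70% attendance and a mean of 2.5 weeks early, preterm women had about 7.3 sessions available and term women 9.6. Expected attendance is 0.70 × 7.3 = 5.1 against 0.70 × 9.6 = 6.7, which is what the simulation gave.

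Median OR per extra session, with the share of runs significantly protective:

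| Mean weeks before 37 | 50% attendance | 70% | 90% |
|---|---|---|---|
| 1.5 | 0.84 (97%) | 0.79 (100%) | 0.61 (100%) |
| 2.5 | 0.81 (99.7%) | 0.74 (100%) | 0.56 (100%) |
| 3.5 | 0.77 (100%) | 0.70 (100%) | 0.52 (100%) |

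The size depends strongly on how much attendance varies between women:
- If all women share one 75% attendance probability, the OR is 0.41–0.47.
- At mean 75% with variation between women, it is 0.61–0.79.
- At mean 50% with variation, it is 0.73–0.86.

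Splitting attendance at five or more sessions gave an OR of 0.10–0.55, significant in 59–100% of runs.

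**3. The same data with a protected exposure**

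- Sessions 1–4 among women undelivered at 29 weeks: OR 1.00–1.02, null rejected in 4–8% of runs.
- Sessions 1–3 only (to 24 weeks): OR 0.98–1.01, falsely protective in about 2–4% (nominal 2.5%).
- Attended divided by scheduled before delivery: OR about 1.00 per 10 percentage points, falsely protective in about 2–6%; rejection in either direction was about 4–8% against a nominal 5%.

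The Monte Carlo standard error of a 5% rate with 300 replicates is √(0.05 × 0.95 / 300) = 1.3 percentage points. The landmark and early-session exposures are therefore close to nominal. The available-session share is close to nominal but slightly high in some settings.

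**The case against.** The strongest reply is that the article never defines the scale. It promises only a variable reflecting attendance level, and a journal article may leave its construction to a fuller document. Table 2's count is a fidelity measure, and a proportion is mentioned elsewhere. A share of sessions available before delivery would largely avoid the bias. This stands, and it rules out saying that a false gradient is certain. It does not dispose of the point: the article fixes the exposure, the outcomes and the purpose, its nearest dose measure is a count, and it states no guard.

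The size is also open to challenge. An OR near 0.4 needs every woman to have the same attendance probability, which is unlikely. That is why a range is given. The direction, and a high false-positive rate for a raw count, persist across the range.

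A reader might infer three stronger things that the article does not support:
- **That the effectiveness result is biased.** That comparison is between Expect With Me patients and the matched cohort and does not use the attendance scale.
- **That the mediation models are certainly affected.** The article refers to participation in sessions but names no mediators, timing or outcomes for these models. The third-trimester survey is not linked to them.
- **That any scale running up to delivery must be dropped.** One with the right denominator is acceptable.

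**Conclusion.** The point holds in conditional form. If dose is a count of sessions to delivery, or a share of ten, the analysis would show a false protective gradient for preterm birth under no effect. The OR per extra session is about 0.4 to 0.86, and the null is rejected in about 95–100% of runs with 900 women and 9.6% preterm. The range rests on assumed attendance level, variation between women and timing of preterm births. It describes the settings tried and is not a bound: more uneven attendance brings the OR nearer 1 and lowers the rejection rate.

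The mechanism itself rests only on the article's timetable, its statement that group care runs to delivery, and preterm birth being a primary outcome. The point is confined to the dose-response analysis among Expect With Me patients and to any mediation analysis built on attendance. It should be fixed before those analyses are run. It does not bear on the main comparison with individual care.

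**What to change.** State in the analysis plan that dose is measured before the outcome can occur, by one of these:

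1. **Landmark:** sessions attended by a fixed gestational age among women still pregnant then, for example sessions 1–4 at 29 weeks.
2. **Weekly delivery model:** discrete-time risk of delivery with lagged, time-updated cumulative attendance.
3. **Simpler alternative:** sessions attended divided by sessions scheduled before delivery.

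Rule out a raw count to delivery and a share of ten sessions. Use the same exposure definition in the structural equation models if they relate attendance to birth outcomes.

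The cost is wording. The online tracking system already records session dates and attendance, and gestational age at delivery comes from the medical record review. Under the landmark, women who deliver before it leave this secondary analysis and attendance after it is not used. The weekly model keeps later sessions but is more work to specify.

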## Cost analyses

The evaluation will include cost analyses [65, 66] comparing *Expect With Me* to individual care, based on patient outcomes (e.g., neonatal intensive care unit admissions and length of stay, emergency department visits). Data from each clinical site’s billing and accounting systems will be used determine patients’ health care charges and actual costs (i.e., amount paid for care collected by the health care facility) including minimum, maximum, median, and interquartile range values of costs for the entire pregnancy through three months postpartum, as well as for the prenatal, childbirth, and postpartum periods separately.

Ordinary least squares (OLS) regressions will be used to test the association between type of care received and maternal and newborn health care costs. Regressions will control for maternal age, race, and other risk factors for adverse birth outcomes. Generalized linear models (GLM) estimates with a gamma distribution and logarithmic link will be used to confirm OLS findings. Alternative approaches to OLS models often are used to account for the long right tail of health care cost distributions. However, OLS results are easier to interpret than many alternative model results. Previous studies of Medicare spending and other health care costs indicated that OLS models perform as well and sometimes better than alternative expenditure models [67, 68].

Costs associated with the provision of group prenatal care from a practice perspective, including start-up and maintenance costs, will also be assessed to inform scalability. Estimates for replication costs will take into account different clinical practice and implementation characteristics.

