To collect organizational data, all clinic staff involved in implementing *Expect With Me* were asked to participate in the process evaluation. To collect extensive data on individual-level outcomes, patients who participate in *Expect With Me* are required to enroll in the evaluation study. We aim to follow more than 1,000 pregnant women through one-year postpartum. Inclusion criteria for patients are as follows: less than 24 weeks pregnant; no severe medical problem requiring individual care only, as determined by the clinical practice; ability to speak English or Spanish; and willingness to participate in the study. Staff at each clinical site explain the study to eligible participants, answer questions, and obtain informed consent. A two-to-one matched cohort of women receiving standard individual care at each clinical site will provide the comparison for the outcome evaluation (two individual care patients for each group care patient). The matched cohort inclusion criteria mirror the study inclusion criteria (e.g., receiving prenatal care at the same clinical practice, entered prenatal care <24 weeks gestation, not transferred out to a high-risk clinic, fluent in English or Spanish, entered prenatal care during the study timeframe). All procedures have been approved by the Yale University Institutional Review Board and Institutional Review Boards at each study site.

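### The cost comparison drops transferred women from the comparison cohort only, as written, and counts only money collected at the site, so it can be biased in a direction the article does not settle

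*Protocol article*

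**What the plan says.** **Cost source and definition (Protocol article, Cost analyses).** The source is the site: "Data from each clinical site’s billing and accounting systems will be used determine patients’ health care charges and actual costs". Actual cost is defined as the "amount paid for care collected by the health care facility", and the period is "for the entire pregnancy through three months postpartum", with the prenatal, childbirth and postpartum periods also shown separately. For sustainability outcomes, Table 2 lists health record reviews, billing records, and provider focus groups and surveys. No payer claims or other source for care given elsewhere is named.

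**Cost model (same section).** "Ordinary least squares (OLS) regressions will be used to test the association between type of care received and maternal and newborn health care costs", with a gamma generalized linear model as confirmation.

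**Who is compared (Organizations and study population).** The comparison criteria are described as mirroring the study criteria. Expect With Me women must have "no severe medical problem requiring individual care only, as determined by the clinical practice". Comparison women must be "not transferred out to a high-risk clinic".

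**Expected losses (Sample size).** The article allows for a "potential 10% drop out rate due to miscarriage, pregnancy complications and changes in life circumstances (e.g., geographic move"), in the passage on recruiting 1,000 group-care women and following them for one year postpartum.

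**Missing data (Analyses).** Multiple imputation, maximum likelihood and sensitivity analyses are planned in general terms. They are not tied to costs.

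**The concern.** There are two separate weaknesses.

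1. **Selection.** Transfer to a high-risk clinic can happen after a woman has entered care. Excluding comparison women on that basis conditions on later risk in one cohort. If Expect With Me women are screened only for severe problems at enrolment, their later transfers remain. Propensity matching on observed characteristics does not undo an exclusion based on what happened afterwards.

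2. **Measurement.** A woman who delivers elsewhere, or whose newborn is treated elsewhere, still has a site total, but it stops when she leaves. That total is a valid number. Imputation acts only on values marked as missing, and the article does not say how an incomplete total would be recognised.

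Lower cost is one leg of the triple-aim claim in the Discussion, and sustainability is said to depend partly on cost. The Background says that much of the saving comes from averted or shorter neonatal intensive care stays and fewer emergency visits, and goes to other departments or payors. A site-only source may miss exactly those items. The same comparison cohort also serves the birth outcomes, so the transfer rule matters there too.

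**Working it through.** The article gives no figure for this bias, so there is nothing to reproduce. The calculations below only show scale.

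**Inputs from the article:** preterm rate 9.6%; reduction of 33–34%; $22,667 saved per preterm birth prevented; cited saving of $750–$890 per birth; 10% drop-out.

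**Assumed inputs (not in the article):** mean episode cost C; share of a leaver's cost that goes unseen, u; share of women transferred, t; preterm rate among transferred women.

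**Step 1. Unseen cost.** Understatement of a mean = share leaving × u. Taking the full 10% as leavers:

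| u | Understatement | C at which it equals $750 |
|---|---|---|
| 25% | 0.10 × 0.25 = 2.5% | 750 / 0.025 = $30,000 |
| 50% | 0.10 × 0.50 = 5.0% | 750 / 0.05 = $15,000 |
| 75% | 0.10 × 0.75 = 7.5% | 750 / 0.075 = $10,000 |

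This is an upper bound. The 10% runs to one year rather than three months, and it includes miscarriage, where a low total may be real and complete. It also supposes that only one arm is affected.

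What biases the comparison is the excess of leavers in one arm: C × excess × u. With u = 50% and C from $10,000 to $20,000:

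- no excess: $0
- 2% excess: $100 to $200
- 5% excess: $250 to $500

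**Step 2. Excluding comparison transfers.** Comparison preterm rate after exclusion = (0.096 − t × transferred preterm rate) / (1 − t).

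| t | Preterm rate if transferred | Rate after exclusion | Fall in comparison mean at $22,667 |
|---|---|---|---|
| 5% | 20% | 0.086 / 0.95 = 9.05% | $124 |
| 5% | 40% | 0.076 / 0.95 = 8.00% | $363 |
| 10% | 20% | 0.076 / 0.90 = 8.44% | $262 |
| 10% | 40% | 0.056 / 0.90 = 6.22% | $766 |

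For comparison, the planned effect is worth 22,667 × 0.096 × 0.33 = $718 to 22,667 × 0.096 × 0.34 = $740 per woman. This step values preterm birth only and works against Expect With Me.

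**Step 3. Both together.** Suppose there is no true effect, Expect With Me transfers are kept and comparison transfers are dropped. Let M be the mean cost of non-transferred women and R the recorded total of a transferred woman. Then

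Expect With Me minus comparison = [(1 − t)M + tR] − M = t(R − M).

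Take t = 5%, M = $15,000, and a true cost for transferred women of 2M, so that R = 2M(1 − u). The difference is 0.05 × 15,000 × [2(1 − u) − 1] = 750 × (1 − 2u):

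- u = 0: +$750 (Expect With Me looks dearer)
- u = 25%: +$375
- u = 50%: $0
- u = 75%: −$375 (Expect With Me looks cheaper)

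The sign depends on how much of a transferred woman's care the site bills, and the article does not say.

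**The case against.** **Silence is not a rule.** The article does not say that transferred Expect With Me women are kept. Pregnancy complications are a listed cause of drop-out, so some may leave the analysed cohort. This stands: a reader might infer that they are retained by design, and the text does not support that. What remains is an exclusion stated for one cohort and not for the other, under criteria described as mirrored.

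**Transfer may be a proxy.** For a cohort assembled from records, transfer may stand in for having a problem that needs individual care. That would explain the wording, but it does not limit the exclusion to what was known at entry.

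**The missing-data plan could cover leavers.** If incomplete totals were set to missing, the general methods would apply, and the planned period-specific costs would help to reveal an absent delivery bill. This also stands. How incomplete episodes are coded is ordinarily left to the analysis plan, and its absence alone would be no finding. The difficulty is that the stated definition of cost yields a number where a missing value is needed.

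**Direction and size.** A reader might infer that truncation falls mainly on Expect With Me and could produce much or all of the cited saving. The documents do not support that. Comparison women also move and use the same billing source, similar losses largely cancel, and excluding costly comparison transfers works the other way. A high-risk clinic might also share the site's billing, in which case a transfer truncates nothing. Every dollar figure above needs inputs that the article does not give.

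**Costs are not primary.** This is true, and it limits the weight of the point.

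**Conclusion.** The point holds in a direction-neutral form. As written, the criteria exclude comparison women for an event after entry and state no counterpart for Expect With Me women. The cost definition also lets incomplete episodes enter the models as complete unless they are recoded. The cost difference can be biased either way. Under the assumptions shown, each mechanism could reach a few hundred dollars per woman: $0 to $500 for unseen cost at up to a 5% excess of leavers, and $124 to $766 for excluded transfers. That is material against a cited saving of $750 to $890, but the net sign and size cannot be determined from the article. It should be corrected. It does not show that any observed saving would be spurious.

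**What to change.** 1. In Organizations and study population, state one analysis-set rule on transfer for both cohorts. It is best defined by information available at cohort entry, so that women transferred later are kept in both. This concerns who is analysed, not how anyone is cared for.
2. In Cost analyses, flag for every woman in both arms whether the delivery and the three-month postpartum window were billed at the site. The record extraction planned after 12 weeks postpartum can help to set the flag.
3. Treat totals without that coverage as incomplete: missing or censored, under the methods already named in Analyses. Add a sensitivity analysis, for example censoring weights or the period-specific costs already planned. Weighting need not be the primary analysis.
4. Report the number of incomplete totals and of transfers by arm.

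The cost is a few sentences, one added flag, some data work for the extra comparison records, and a somewhat wider confidence interval.
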